**5.4.3. Administrative data**

Date and cause of death will be ascertained from **Vital Records**, as well as contacts listed on locator forms for those participants lost-to-follow-up.

**SUDTx data**, from 4 months pre-enrollment to study completion, will be obtained with appropriate HIPAA/CFR-42 release.

**5.4.4. Data Management**

Data will be maintained in MS Access (tracking and administrative data), QDS warehouse manager (survey data). All data will be backed up nightly at the study site based on San Francisco Department of Public Health protocols.

# ADVERSE EVENTS MANAGEMENT

## 6.1 Definition of Adverse Events and Serious Adverse Events

For this study, we will record and report only adverse events (Aes) directly related to study participation. We will not report opiate overdose events as adverse events.

In the event of study-related Aes, we will use the DAIDS Table for Grading the Severity of Adult and Pediatric Adverse Events version 1.0, December 2004 (Clarification dated August 2009) available at: <http://rsc.tech-res.com/safetyandpharmacovigilance/>

We will record and report all study-related Aes in accordance with these NIH guidelines. Safety monitoring will include the assessment, follow-up, and reporting of clinical Aes and serious Aes (SAEs), and abnormal laboratory results. Each AE will be classified by the study clinician as serious or non-serious, and appropriate reporting procedures will be followed.

A ***serious AE*** is any untoward medical occurrence related to study activities:

- results in death,
- is life-threatening (defined as an event in which the patient was at risk of death at the time of the event; it does not refer to an event which hypothetically might have caused death if it were more severe),
- requires inpatient hospitalization or causes prolongation of existing hospitalization,
- results in persistent or significant disability/incapacity,
- is a congenital anomaly/birth defect,
- is an important medical event (defined as a medical event(s) that may not be immediately life-threatening or result in death or hospitalization but, based upon appropriate medical and scientific judgment, may jeopardize the patient or may require intervention (e.g., medical, surgical) to prevent one of the other serious outcomes listed in the definition above.

An unexpected event is one that is not described with respect to nature, severity, or frequency in the current protocol.

Adverse events classified as “serious” require expeditious handling and reporting to comply with regulatory requirements.

**6.2 Management of SAEs and other study risks:** Participants requiring acute medical care will be treated on-site by a clinician, and, once stabilized, taken to the appropriate hospital for care (most likely, depending on availability, San Francisco General Hospital which is five minutes by ambulance). All participants will be provided with a 24-hour phone number through which the study clinician may be contacted to answer questions or to provide direction in case of emergency**.**

**6.3 Reporting of SAEs**: All Aes that are serious and meet the reporting criteria will be reported to the UCSF IRB in writing, within 10 working days.

SAE reporting will include a narrative which will provide details of relevant screening measures, medical history and physical, treatment compliance, participant reports of SAEs, and any other required information. The completed SAE form will contain: subject’s ID#, gender, age, the title and date of the SAE, and narrative explanation. The SAE form tracks how the research staff was notified of the event, dates of consent, randomization, study screening for inclusion/exclusion, study treatment received, other relevant clinical information, dates and circumstances of the hospitalization/death, whether alcohol or drugs were known to be involved, and participant status at last clinical or research contact. The investigators will state whether the event was expected and assess its relatedness to the study intervention. A summary report of all Aes (including SAEs) will be submitted to the IRB and to NIDA in the annual progress report.

Collection of complete information concerning SAEs is extremely important. Follow-up information which becomes available as the SAE evolves, as well as supporting documentation (e.g., hospital discharge summaries and autopsy reports), should be collected subsequently, if not available at the time of the initial report, and immediately sent using the same procedure as the initial SAE report.

###### An expedited reporting of SAE will adhere to the following guidelines:

1. Apply regardless of the investigator’s assessment of the relatedness of the SAE to the intervention under study.
2. Apply equally to trials requiring an IND and those not requiring an IND.
3. Apply to any SAE that occur during the post-treatment observation period defined by the protocol.
4. Apply to suicidal or homicidal behavior that causes an SAE in the subject or someone else (*e.g.* hospitalization or death).
   1. **CHANGES TO STUDY PROTOCOL**

**7.1 Reporting of IRB actions to NIDA:** Through the study project officer, NIDA will be informed of IRB actions regarding the study. When significant revisions to the protocol are planned, IRB communications will be forwarded to the NIDA PO.

**7.2 Report of changes or amendments to the protocol:** All changes and amendments to the study protocol will require IRB approval prior to their implementation. When appropriate, the NIDA PO will be informed of changes or amendments to the study protocol.

**7.3 Trial stopping rules:** There are no formal trial-stopping rules for this study. No formal interim efficacy analysis will be conducted.

If it becomes clear that the trial puts undue safety risk on study participants, outcomes are poor, or the trial will not achieve its enrollment goals, consideration will be given to stopping the trial, after consultation with the IRB and NIDA PO.

The overall safety risk to study participants will be determined through regular monitoring procedures. Safety issues will be evaluated as they arise; participants are given the pager number of the clinician on call which they can page in the event of an emergency or safety risk. Study clinicians will consult with [name], the medical director and Principal Investigator, on these safety issues on a case-by-case basis as they are reported by the participant. Non-urgent clinical issues that arise during the course of the study are discussed by the team’s research clinicians at the next weekly meeting with the PI [name]. During weekly meetings, study clinicians will review all the safety issues and incident adverse events (including lab abnormalities) for the study overall, by system category, and by possible relationship to the behavioral intervention. The PI will alert the DMSB and the NIDA P.O. immediately if at any point the team observes an unexpected frequency of serious Aes possibly related to the intervention.

**7.4 Disclosure of conflicts of interest:** Staff are required to disclose any financial conflicts of interest with the study. Signed documentation of conflicts of interest by study investigators (or lack thereof) will be provided to the IRB as required by the initial and continuing review process.

# STATISTICAL CONSIDERATIONS

## Analysis Objectives

### Analysis Objectives

The primary objectives of this study are:

- To determine the feasibility of a randomized trial with REBOOT.
- To determine acceptability of REBOOT.
- To evaluate the influence of egocentric social network characteristics on overdose events and naloxone use.

The exploratory objectives of this study are:

- To determine the preliminary efficacy estimates of REBOOT in decreasing overdose events (non-fatal or death), decreasing frequency of modifiable overdose / drug-related HIV risk behaviors, and increasing days of abstinence from illicit opioids and in substance use treatment.

## Analysis Conventions

All individual subject data will be listed as measured. All statistical summaries and analyses will be performed using STATA^®^ software.

## Demographic Data and Baseline Characteristics

Demographic and baseline characteristics will be summarized using standard descriptive methods by treatment group and overall.

Demographic data will include sex, self-identified race/ethnicity, and age.

## Data Analysis

### Primary Analysis

Specific Aim 1: To determine feasibility of a randomized trial with REBOOT, we will calculate screening and visit completion rates from the study database, with exact 95% confidence intervals (Cis), overall and by arm. Between-group differences will be assessed using Fisher’s exact and Wilcoxon ranksum tests. We will calculate Kaplan-Meier curves for time to dropout, by group, and test for differences using the log-rank test.

Specific Aim 2: To determine acceptability of REBOOT, we will calculate counseling completion rates from the study database by visit, and tabulate the proportions of active arm participants attending 0-4 counseling sessions. Via CAPI, we will inquire about participant satisfaction with the intervention and belief that it affected their drug use behaviors; responses will be presented as means, medians, or proportions, as appropriate, with 95% Cis.

Specific Aim 3: To evaluate the influence of egocentric social network characteristics on overdose events and naloxone use, we will use GEE Poisson models with robust standard errors to evaluate the association between network size, evaluated at baseline and each return visit, and numbers of experienced and witnessed overdose events in the same period; zero-inflated models will be used if needed. Results from this analysis will inform study design of a full efficacy trial and determine if randomization stratified by network size or targeted sampling strategies to ensure diversity in network size are needed. In addition, we will explore the influence of homophily and assortativity on experienced and witnessed overdose events using similar methods. Newman’s method will be used to calculate assortativity coefficients, a measure of the degree of demographic and risk behavior similarity within participants’ egocentric networks.

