### Enrollment Visit

Enrollment tests and procedures will be completed prior to enrollment and receipt of the first counseling session.

On the enrollment visit, participants will be randomized to receive the behavioral intervention (n=40) or TAU (n=20). **Randomization** will be 2:1 using permuted blocks of randomly selected sizes 3 and 6.

Participants will provide a urine toxicology test, and will undergo the baseline CAPI followed by initial counseling for the treatment group and TAU for the reference group. The next visit will be scheduled and participants will be compensated for their time.

Subjects will be compensated $30 for the enrollment visit.

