### 5.4.2. Computer Assisted Personal Interview (CAPI)

All participants will receive a CAPI at enrollment and months 4, 8, 12, and 16. The CAPI will **always** be conducted by a staffperson blinded to participant’s study arm and prior to administration of the REBOOT intervention or control arm procedures.

The CAPI includes demographic information (enrollment only), drug use history (enrollment only), extensive opiate overdose questions, drug use and drug-related risk behaviors, partner-by-partner data on injection/substance use/HCV status, quality of life scale (EQ5-D), Center for Epidemiologic Studies Depression Rating Scale, and Severity of Dependence Scale and participant satisfaction with treatment.

Primary and secondary outcome variables will be obtained from standardized scales assessed using CAPI to minimize underreporting of risk activities and enhance standardization.^4^ We will utilize the same overdose measures as in the pilot, which were developed in collaboration with other investigators (Drs [name], [name], [name], and [name]) to maximize comparability among overdose studies.

- **Quality of Life Surveys:** The quality of life scale included in this study is the EQ5-D. It will be completed by participants at enrollment and months 4, 8, 12 and 16 regardless of study arm. The Quality of Life Survey will be included in the CAPI.
- **Depression Rating Scale** The depression rating scale included in this study is the Center for Epidemiologic Studies Depression Rating Scale. It will be completed by participants at enrollment and months 4, 8, 12 and 16 regardless of study arm. The Depression Rating Scale will be included in the CAPI.
- **Severity of Dependence Scale:** The Severity of Dependence Scale will be completed by participants at enrollment and months 4, 8, 12 and 16 regardless of study arm. The Severity of Dependence Scale will be included in the CAPI.

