## Sample Size

**Sample size justification:** The sample will provide typical precision for a pilot study of feasibility and acceptability outcomes. Specifically, we will be able to estimate the mean of continuous outcomes within margins of sampling error (MSEs; half-widths of 95% confidence intervals) of 0.32 standard deviations (SDs) within the active arm, and 0.26 SDs overall; proportions will be estimated within MSEs of 9-16 percentage points in the active arm and 8-13 percentage points overall. For Aim 3 and the exploratory analyses of treatment efficacy, precision and power will be low, as is also typical for a pilot study. In designing the full-scale trial, these exploratory results will be cautiously interpreted in the light of confidence intervals, plausibility, and prior results from the literature.

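### As worded, a per-participant Newman coefficient from ego-to-partner ties is either constant, or never positive and undefined at full similarity, so it is not the similarity measure Aim 3 describes

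*Protocol*

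**What the plan says.** Under Primary Analysis, Specific Aim 3, the main analysis concerns network size: "we will use GEE Poisson models with robust standard errors to evaluate the association between network size, evaluated at baseline and each return visit", with counts of experienced and witnessed overdoses as outcomes. The protocol then adds a further, exploratory element: "we will explore the influence of homophily and assortativity on experienced and witnessed overdose events using similar methods". The measure is named next: "Newman’s method will be used to calculate assortativity coefficients, a measure of the degree of demographic and risk behavior similarity within participants’ egocentric networks". The same text stands in the synopsis under Statistical Methods.

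The section on the Computer Assisted Personal Interview (CAPI) describes the network data as "partner-by-partner data on injection/substance use/HCV status". Ties between one partner and another are not mentioned anywhere. The section on demographic data lists sex, race/ethnicity and age. The Sample Size section concedes that "For Aim 3 and the exploratory analyses of treatment efficacy, precision and power will be low".

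**The concern.** Newman's coefficient compares the mixing seen across many nodes with the mixing expected from the marginal distributions. It is meant for a whole network. The protocol places it inside each participant's own network and uses it as an exposure, by methods like those for network size. A regression exposure must vary between participants, so the natural reading is one coefficient per participant (and visit).

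With only the participant (ego) and the partners (alters) he or she reports on, each network is a star: every tie has the ego at one end. There the ego's side of the mixing table has no variation of its own, and the coefficient loses its usual meaning. At stake is whether the assortativity covariate measures similarity at all, and whether participants whose partners are all like them stay in the model.

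**Working it through.** **Inputs.** From the protocol: the method, its use as an exposure, the partner-by-partner data, and 40 + 20 = 60 participants. Not given, so assumed: the number of partners k (2, 3, 5, 10), the share p of partners who match the ego, and a star network. The protocol gives no figure for assortativity. Its precision figures for means reproduce as t/√n (0.320 SD for n = 40, 0.258 SD for n = 60) but do not bear on this point.

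**Formula.** For categories, r = (Σe_ii − Σa_i b_i)/(1 − Σa_i b_i), where e is the table of tie proportions and a, b are its margins.

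**Directed ties, ego to partner.** All mass lies in the ego's row, so a = 1 for the ego's category and b = p there. Then Σe_ii = p and Σa_i b_i = p, so r = (p − p)/(1 − p) = 0 for every p < 1, and 0/0 at p = 1.

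**Undirected ties, any number of categories.** Let q_j be the share of partners in each other category and Q = Σq_j². Then Σe_ii = p and Σa_i² = [(1 + p)² + Q]/4. The numerator of r is −[(1 − p)² + Q]/4, which cannot be positive. At p = 1 both numerator and denominator are 0.

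**Undirected, binary trait.** Here Q = (1 − p)², so r = −(1 − p)/(1 + p):

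| Partners alike (of 5) | 0 | 1 | 2 | 3 | 4 | 5 |
|---|---|---|---|---|---|---|
| r | −1.00 | −0.67 | −0.43 | −0.25 | −0.11 | undefined |

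The value rises strictly with p but unevenly: from 0 to 1 alike it moves 0.33, from 3 to 4 alike it moves 0.14. With 9 of 10 partners alike, r = −0.05.

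**Undirected, three categories, 10 partners.** r no longer depends on p alone.
- 5 alike, others split 3 and 2: Σa² = (2.25 + 0.13)/4 = 0.595, so r = (0.5 − 0.595)/0.405 = −0.235.
- 6 alike, other 4 in one category: Σa² = (2.56 + 0.16)/4 = 0.68, so r = (0.6 − 0.68)/0.32 = −0.25.

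The less similar network gets the higher score.

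**Scalar trait such as age.** Newman's version is the correlation over ties. For an undirected star, r = −(d²/4)/(d²/4 + s²/2), where d is the partners' mean minus the ego's value and s² is the variance among partners.
- Ego 40, all partners 41: d = 1, s² = 0, r = −1.
- Ego 40, partners 20 and 60: d = 0, s² = 400, r = 0, the maximum.

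Near-identical ages take the lowest score and widely different ages the highest. With directed ties the ego side has no variance and r is undefined for everyone.

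**How many would be undefined (categorical trait).** If partners match independently, the share is p^k:

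| p | k = 2 | k = 3 | k = 5 | k = 10 |
|---|---|---|---|---|
| 0.5 | 25% | 13% | 3% | 0.1% |
| 0.8 | 64% | 51% | 33% | 11% |
| 0.9 | 81% | 73% | 59% | 35% |

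At p = 0.8 and k = 5 that is 0.328 × 60 ≈ 20 participants, all from the fully homophilous end.

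**Contrast cases.** Pooled over 60 egos with 5 partners each, one simulated sample gave r = 0.64 with an 80% same-type probability, and another gave −0.06 with 50%: sensible values, but one per sample. With partner-partner ties (assumed tie probability 0.8 for the same type, 0.05 for different types, 4 to 10 partners), r was positive in 81% of simulated networks in which it was defined, and reached 0.66.

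**The case against.** A reader might infer that the coefficient is uninformative, that it reverses the direction of any association, or that the analysis cannot work. The documents do not support that much. With undirected ties and a binary trait, r is a strictly increasing function of p wherever it is defined. A log-linear model does not care that a covariate is negative, and a higher r still means more similar partners. Only directed ties give a constant, and the protocol does not say that ties are directed.

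The star structure and the per-participant calculation are also inferences. The CAPI is summarised in one phrase, and details are deferred to a procedures manual that is not shown. Partner-partner ties are not excluded, and with them positive values are possible. The text could be read as a participant-level homophily share in the model with a pooled Newman coefficient beside it. It could also be argued that tie direction, pooling and handling of undefined values belong in a statistical analysis plan.

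These points limit the claim but do not remove it. The protocol itself fixes the method, the level and the interpretation, so this is not merely missing detail. The per-participant star is the reading best supported by its words. The binary-trait defence does not extend to race/ethnicity or age, although the stated measure covers demographic similarity. A pooled coefficient escapes the algebra but cannot serve as a covariate.

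Nor does this undermine Aim 3 as a whole. The assortativity work is an exploratory addition, the design decisions named there concern network size, and low precision is already conceded.

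**Conclusion.** The point holds in a limited form. If r is computed per participant from ego-to-partner ties alone, it is 0 throughout (directed) or never positive (undirected). For categorical traits both forms are undefined when all partners match the ego. Missingness then depends on the exposure itself. It could be slight or affect most participants, depending on partner numbers and similarity that the protocol does not give. For multi-category or scalar traits the undirected coefficient can rank less similar networks above more similar ones, so it is not the similarity measure it is said to be.

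The algebra is exact. The conclusion rests on two readings of the protocol: that no partner-partner ties are collected, and that one value per participant is intended. It is worth correcting before analysis, but its reach is the exploratory homophily and assortativity part of Aim 3. The network-size model stands.

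**What to change.** In Specific Aim 3 and in the matching synopsis text:

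- Use as the participant-level, visit-level covariate the proportion of partners sharing the ego's attribute, or the E-I index (external minus internal ties over all ties, which equals 1 − 2p). For scalar traits use the mean absolute ego-partner difference; in the age examples above it is 1 and 20, the right order. Include the ego's own attribute in the model.
- Report Newman's r only as a pooled description for each attribute, with a confidence interval from bootstrapping participants.
- Alternatively, if partner-partner ties are collected, say so, and say how undefined values will be handled.

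The cost is a change of wording and a simpler calculation, with no new visits and no new data for attributes already recorded on partners. The share is defined for anyone with at least one partner, including p = 1; participants with no partners at a visit need a stated rule. The drawback is that a per-person share is not fully corrected for chance. The own-attribute term absorbs an additive shift in the expected share but does not reproduce Newman's division by one minus the expected value, so it adjusts only in part.

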### Exploratory Analyses

Exploratory analyses include preliminary efficacy estimates of REBOOT in decreasing overdose events (non-fatal or death), decreasing frequency of modifiable overdose / drug-related HIV risk behaviors, and increasing days of abstinence from illicit opioids and in substance abuse treatment.

## Sample Size

**Sample size justification:** The sample will provide typical precision for a pilot study of feasibility and acceptability outcomes. Specifically, we will be able to estimate the mean of continuous outcomes within margins of sampling error (MSEs; half-widths of 95% confidence intervals) of 0.32 standard deviations (SDs) within the active arm, and 0.26 SDs overall; proportions will be estimated within MSEs of 9-16 percentage points in the active arm and 8-13 percentage points overall. For Aim 3 and the exploratory analyses of treatment efficacy, precision and power will be low, as is also typical for a pilot study. In designing the full-scale trial, these exploratory results will be cautiously interpreted in the light of confidence intervals, plausibility, and prior results from the literature.

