# SUBJECT POPULATION

## Number of Subjects and Subject Selection

At least 60 subjects will be enrolled in this study, potentially up to 70, to ensure at least 60 people who inject drugs are included.

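### Section 8.5's margins assume all 40 and 60 participants are observed: optimistic for CAPI-based acceptability items and continuous follow-up outcomes, and silent on the 20-person TAU arm behind Aim 1's by-arm results

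*Protocol*

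**What the plan says.** Protocol section 8.5 (Sample Size) describes precision through "margins of sampling error (MSEs; half-widths of 95% confidence intervals"). For means it gives "0.32 standard deviations (SDs) within the active arm, and 0.26 SDs overall". For proportions, "proportions will be estimated within MSEs of 9-16 percentage points in the active arm and 8-13 percentage points overall". It names no interval method, no range of true proportions and no retention rate. It gives no margin for TAU.

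The Enrollment Visit section fixes the arm sizes: "participants will be randomized to receive the behavioral intervention (n=40) or TAU (n=20"). Section 4 (Number of Subjects and Subject Selection) adds: "At least 60 subjects will be enrolled in this study, potentially up to 70, to ensure at least 60 people who inject drugs are included".

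Section 8.4.1 sets the methods. For Aim 1, "we will calculate screening and visit completion rates from the study database, with exact 95% confidence intervals (Cis), overall and by arm", followed by Fisher, Wilcoxon and log-rank comparisons of the arms. Aim 2 combines counseling attendance, taken from the study database, with satisfaction and perceived effect, asked in the CAPI. Section 5.4.2 places every CAPI before that visit's counseling or control procedures.

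The caution in section 8.5 is limited in scope: "For Aim 3 and the exploratory analyses of treatment efficacy, precision and power will be low". It adds that "these exploratory results will be cautiously interpreted in the light of confidence intervals", among other considerations. Aim 3 and most treatment-effect analyses use Poisson models with robust standard errors.

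**The concern.** Feasibility and acceptability are primary objectives, and section 8.5 is the only place where the reader learns how well they will be estimated. Three things are left out.

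- **Loss to follow-up.** The enrollment CAPI comes before any counseling, so it cannot measure satisfaction with it. Every satisfaction answer comes from a month 4-16 visit, and its n is the number who return. Time to dropout is itself an Aim 1 outcome, so full retention is not taken for granted elsewhere in the protocol.
- **The smaller arm.** Aim 1 promises by-arm intervals and between-arm tests, which depend most on 20 TAU participants. The margins shown leave that arm out, and the low-power warning does not reach these tests. A non-significant retention test could then be given more weight than it can bear when the full trial is designed.
- **Interval coverage.** The exploratory efficacy results are to be read partly from their confidence intervals. Sandwich errors without correction tend to be too small when one arm has 20 clusters.

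**Working it through.** **Inputs from the protocol:** 40 active, 20 TAU, 60 in total, up to 70 allowed; margins are 95% half-widths; exact intervals for Aim 1. **Assumed here, because the protocol gives no values:** proportions from 0.5 to 0.9, retention of 70-90%, the completion rates in the power check, and the event rates and overdispersion in step 6.

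**1. Reproducing the stated figures.** Means, t(0.975, n-1)/√n:
- n=40: 2.023/6.325 = 0.320
- n=60: 2.001/7.746 = 0.258

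Proportions, using 2·√(p(1-p)/n) at p = 0.9 and 0.5:
- n=40: 9.49 and 15.81 points
- n=60: 7.75 and 12.91 points

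These round to 0.32, 0.26, 9-16 and 8-13, so the full randomised numbers were used. With a multiplier of 1.96 the means alone would also fit n of 37-38 and 55-59. Even that reading would allow for very little loss.

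**2. Does the exact method change the picture?** Clopper-Pearson half-widths:

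| Group | 90% observed | 50% observed | Stated |
|---|---|---|---|
| Active, n=40 | 36/40: 10.4 | 20/40: 16.2 | 9-16 |
| Overall, n=60 | 54/60: 8.4 | 30/60: 13.2 | 8-13 |
| TAU, n=20 | 18/20: 15.2 | 10/20: 22.8 | none |

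Only the lower active-arm figure moves, from 9 to about 10. At 37/40 the exact half-width is 9.4, so even that depends on the assumed 0.9. Exact intervals are asymmetric at high completion: 36/40 gives 76.3-97.2%, with the lower limit 13.7 points below the estimate.

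**3. Where loss reduces n.** Visit completion and counseling attendance naturally count everyone randomised, so a dropout is a non-completer and not a missing value. Screening rates rest on those screened. CAPI satisfaction items and continuous follow-up outcomes have only the returning participants.

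**4. CAPI-based margins with 60 enrolled.** Means by t/√n; worst-case proportion by Clopper-Pearson at 50%:

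| Retention | Active n | SD | Points | Overall n | SD | Points |
|---|---|---|---|---|---|---|
| 100% | 40 | 0.32 | 16.2 | 60 | 0.26 | 13.2 |
| 90% | 36 | 0.34 | 17.1 | 54 | 0.27 | 13.9 |
| 80% | 32 | 0.36 | 18.1 | 48 | 0.29 | 14.8 |
| 70% | 28 | 0.39 | 19.4 | 42 | 0.31 | 15.8 |

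With 70 enrolled (about 47 active), 85% retention leaves 0.85 × 70 = 59.5 overall and about 40 active, which restores the stated margins.

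**5. Aim 1 between arms.** At 18/20 the exact TAU interval is 68.3-98.8%. Two-sided Fisher power at 5%, enumerated over all outcomes for 40 active against 20 TAU:
- 90% vs 70%: 44%
- 80% vs 60%: 32%
- with TAU as the higher arm: 37% and 29%

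**6. Robust standard errors.** Null simulation of the treatment contrast in a Poisson model: 40 vs 20 participants, four periods, 6% dropout per period, 0.1-0.4 events per period, gamma heterogeneity variance 1-4, 8,000 runs per setting. Type I error was 5.9-10.5% with uncorrected errors and a normal reference, and 3.9-8.7% with Mancl-DeRouen errors and a t reference. A separate simulation at the same arm sizes, also with assumed rates and overdispersion, gave 5.4-10.1% and 3.8-8.1%. Uncorrected 95% intervals therefore cover about 90-95%.

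**The case against.** No stated figure is miscalculated, and that stands. A reader might infer from the word exact in Aim 1 that the proportion margins hold only under a normal approximation. The documents do not support this: exact half-widths of 16.2, 13.2 and 8.4 round to the stated 16, 13 and 8, and the one remaining difference is about a point at a proportion the protocol never specifies.

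A reader might also infer that feasibility precision as a whole is overstated. It is not, for the denominator reason in step 3.

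Sixty is a minimum, and 70 would offset about 15% loss. That is true as far as it goes. However, the extra places exist to secure 60 people who inject drugs, may not be filled, and are not used in section 8.5.

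The by-arm intervals and Kaplan-Meier curves will show the TAU arm's imprecision, and nothing in the protocol says a non-significant test will be taken as no difference. This is fair. The point is that the warning is missing where the reader would look for it, not that a misreading is planned.

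Finally, section 8.5 claims no precision for the GEE models and already urges caution, and a small-sample correction may be set in an analysis plan that is not shown. If so, that part is already met. The event rates behind the coverage figures are assumptions, and the correction only reduces the problem. It concerns treatment contrasts more than Aim 3, which relates network size to events across all participants.

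**Conclusion.** The point holds in limited form. The margins in section 8.5 are right for complete data and allow for no loss. For CAPI-based acceptability items and continuous follow-up outcomes, the overstatement is modest: at 80% retention of 60, 0.03-0.04 SD and about 2 points in the worst case. At 70% it is about 3 points. The size depends on a retention rate the protocol does not give. Visit and counseling completion are not affected.

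The TAU gap is larger. Its exact margin of about 15-23 points is wider at each end than either stated range, and a 20-point difference in completion would more often be missed than found at the rates examined. The low-power caveat should cover that comparison.

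The GEE part is secondary and rests wholly on assumed event rates and overdispersion. Under them, coverage falls short of nominal by up to about five points. None of this calls for a larger pilot.

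**What to change.** In section 8.5:

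- State the interval method and the range of proportions behind the margins.
- Give the CAPI-based margins over an assumed 70-90% retention of 60 enrolled: active 0.34-0.39 SD and worst-case exact 17-19 points; overall 0.27-0.31 SD and 14-16 points. Note that enrollment up to 70 would offset about 15% loss.
- Add the TAU margin, about 15-23 points exact.
- Extend the low-power caveat to Aim 1's between-arm comparisons.

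In section 8.4.1, report the difference in completion between arms with its 95% interval beside the Fisher and log-rank results.

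For the GEE models, specify a small-sample-corrected robust variance, such as Mancl-DeRouen, with a t reference, here or in the analysis plan. State that this reduces undercoverage without fully removing it.

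The cost is wording, slightly less favourable precision figures and slightly wider model-based intervals. Enrollment, visits and procedures stay as they are.
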